All participants will be provided a self-swabbing kit from the study team that includes Dacron swabs and test tubes with transport media (TM) which are already labeled with the participants' hospital number, along with written instructions. Participants will be asked to take one nasal self-swab, and to place it in the refrigerator in a separate test tube filled with 1-3ml of TM. Participants will then be asked to describe the procedure to ensure they understand the full technique and will be guided appropriately. Participants will be given a study card with their study ID number and assigned health volunteer's telephone number. Participants who experience an ARI, defined as new onset of cough or worsening of chronic cough, will be asked to take a self-swab as soon as possible and then to call their assigned health volunteer to make an appointment to have their swab collected and answer some questions for the ARI/SARI Episode Questionnaire at the time of the appointment (which will be within 24 hours). The assigned health volunteer will bring an ice box and new Dacron self-swab kit to the sick participant's home, and the specimen will be transported in the ice box by the health volunteer to the sub-district health center for temporary storage. Health volunteers will also conduct the Functional Status Questionnaire three to four weeks after the onset of a participant's ARI or SARI and the Outcomes and Costs of ARI Questionnaire 1 week after the participant recovers which will be monitored through the weekly calls and by the study team. If a participant is very ill due to an ARI and needs assistance in taking a nasal self-swab, they can ask their assigned health volunteer for help in obtaining the specimen. Health volunteers will also be trained to contact their assigned participants weekly to identify ARI events that they have not been notified of already and to take a weekly questionnaire. They will attempt three contacts, by phone or in person, at different times of the day before considering the participant to have missed the week. In the case of an ARI event, participants who have not yet taken a self-swab will be asked to self-swab immediately.

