For any participant that does not have a phone or for participants who have a phone without a working signal, we will have the health volunteer follow-up with them on a weekly basis by making household visits instead of a weekly call and rely on this method for collection of all data. If a participant without a working phone develops an ARI or SARI during the week and is able to send someone to the health volunteer to let them know, the health volunteer can also follow-up with the patient using the electronic ARI/SARI Episode Questionnaire, but this is not mandatory for participants without a working phone. If the participant needs to get in touch

with the researcher, the health volunteer will be trained to use their phone to call the researcher for them. When health volunteers transport the specimens to the sub-district health center/district hospital, they will place them inside a refrigerator with a controlled temperature of 2-8°C. Research nurses at the district hospital will be trained to transport the swabs from the refrigerator into the liquid nitrogen tank once a day to keep the specimens below -70°C until transported to NIH.

One research nurse from each health center will be responsible for the enrolled participants within their sub-district. In the event that a participant becomes very ill and goes to the hospital or sub-district health center for treatment of an ARI or SARI, the research nurse at the sub-district health center or district hospital will collect a nasopharyngeal swab from the participant and store it in a refrigerator as outlined in appendix 5a. They will administer the ARI/SARI questionnaire (for health centers) and call the study team to notify them about the participant's visit. The study team will inform the participant's assigned health volunteer so the health volunteer can monitor the participant and take the Functional Status Questionnaire and the Outcomes and Costs of ARI Questionnaire after the participant recovers at the appropriate time period. The nasopharyngeal swabs will also be placed inside a liquid nitrogen tank at the sub-district health centers and district hospitals once a day by trained study team personnel. The nurses at the district hospitals will also collect a nasopharyngeal swab for all participants with COPD who come to the COPD clinic due to an exacerbation.

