## **7.9 Data Analysis**

In order to evaluate the primary research question – the vaccine effectiveness of the inactivated trivalent IIV3 vaccine in the elderly - we will use Poisson regression with person-time at risk as an offset. The outcome variable will be the number of influenza associated ARI or SARI events in each given year of life among 2 groups, elderly who have been vaccinated with IIV3 and elderly who have not. The resulting count data will account for multiple outcomes in the same participant. We will also employ GEE methodology to the Poisson regression to account for geographical clustering by cases and correlation between outcomes in individuals with repeated measures. We can control for other predictive variables that may be associated with

underlying disease such as age, co-morbidities and distance to health facility. To reduce any potential non-random loss-to-follow up bias, we will use propensity score matching in addition to controlling for confounders. To address the other primary study question regarding cost, we will obtain estimates of direct and indirect costs from each of the groups and apply differences to the adjusted risks to arrive at the adjusted cost differences between elderly who have been vaccinated and elderly who have not been vaccinated.

In order to measure the effect ARI and SARI have on functional status (secondary objective 2.1) we will compare change in functional status among those that did and did not experience ARIs or SARIs by matching participants to one control when they become sick to see if there is a significant difference in functional status measurements. We will use a nested case control study to compare the two groups. By matching those who experienced a first ARI or SARI with those who had not on age ( $\pm 5$  years), sex, influenza vaccination and most recent functional status measurement ( $\pm 1$  point), we can account for unknown confounders that may cause a change in functional status while controlling for known confounders.

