## **Limitations**

The main limitation of this study is its limited generalizability to Thailand. While we are able to obtain a representative sample of Nakhon Phanom Province, the people in NP may be different than people from other parts of Thailand. Another limitation is sampling bias. The study's sample may be biased since healthier people are usually more willing to participate in studies compared to people who are more ill, which would not represent the target population of all types of elderly people. In order to diminish the potential of sampling bias, our inclusion criterion includes all elderly despite illness type.

It is possible that not all respiratory events in the enrolled elderly will be captured, due to inability to communicate, misunderstanding and even memory loss. To a large extent, a lot of the success for this project may rely on the relationship between the household and health volunteer and role of the caregiver for participants greater than 80 years of age. Another limitation to our study is that baseline enrollment data and weekly follow-up data is relying heavily on self-report. It is possible for participants to be unaware of whether they have certain underlying co-

morbidities if they do not regularly visit the physician, it is possible for them to under or overestimate their functional status, and it is possible for them to forget to take a nasal self-swab or remember that they even experienced an ARI or SARI. In order to mitigate these potential issues, we are using a reliable and sensitive functional status questionnaire and following-up with participants weekly in case they forget to call us.

Although Thailand provides free vaccinations for elderly, there are not enough purchased to vaccinate all elderly in Thailand. Due to the limited number of vaccines, elderly that are sicker and see health care professionals more often are more likely to become vaccinated than those who are healthier. The elderly who join our immunogenicity study will most likely be sicker than the general population and are more likely to be immunocompromised. Because of this selection bias, our immunogenicity study will most likely show a lower rate of seroprotection among the elderly than what is actually representative of the average elderly population.

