| 4                                                                                                                                | In general, compared to other people your age, would you say that your health is poor, fair, good, very good or excellent? | 1 Very poor
2 Bad
3 Fair
4 Good
5 Very good or excellent
77 Do not know
99 Declined to answer |      |
| 5                                                                                                                                | Have you experienced any severe illness in the last year?                                                                  | 1 Yes
2 No
77 Do not know
99 Declined to answer                                                        |      |
| 6                                                                                                                                | Did you have to be hospitalized for any illness in the last year?                                                          | 1 Yes
2 No
77 Do not know
99 Declined to answer                                                        |      |

|                                                                                              |                                                                                                                                                                                                              |                                                                                                                                                                                      |                            |                          |                            |                          |                                                           |
|----------------------------------------------------------------------------------------------|--------------------------------------------------------------------------------------------------------------------------------------------------------------------------------------------------------------|--------------------------------------------------------------------------------------------------------------------------------------------------------------------------------------|----------------------------|--------------------------|----------------------------|--------------------------|-----------------------------------------------------------|

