|                                                                                                                                                                   |                                       |                                                                                                                                                                                    |                                                        |
|-------------------------------------------------------------------------------------------------------------------------------------------------------------------|---------------------------------------|------------------------------------------------------------------------------------------------------------------------------------------------------------------------------------|--------------------------------------------------------|
| Now I would like to ask you about your health history. Please tell me whether you have been diagnosed by a physician with any of the following conditions: |                                       |                                                                                                                                                                                    |                                                        |
| 33                                                                                                                                                                | Chronic lung disease                  | 1 Yes
2 No
77 Do not know
99 Declined to answer                                                                                                                           | If no,
           skip to
           35 |
| 34                                                                                                                                                                | If yes, please specify:               | 1 COPD
2 Emphysema
3 Asthma
4 Fibrosis
5 Chronic bronchitis
6 Tuberculosis
7 Lung cancer
8 Other
Specify: _____
77 Do not know
99 Declined to answer |                                                        |

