| 6                                                                                                                                                                                                           | Nasal discharge/congestion?                                              | 1 Yes
2 No
77 Do not know                                                                                                                  |  |
| 7                                                                                                                                                                                                           | Sore throat?                                                             | 1 Yes
2 No
77 Do not know                                                                                                                  |  |
| 8                                                                                                                                                                                                           | Is the patient hospitalized or does the patient need to be hospitalized? | 1 Yes
2 No
77 Do not know                                                                                                                  |  |
| 9                                                                                                                                                                                                           | When did this illness begin?                                             | 1 Today
2 Yesterday
3 2 days ago
4 3 days ago
5 4 days ago
6 5 days ago
7 6 days ago
8 7 days ago
9 More than 7 days ago |  |
| If answer is no for question 2 and 3, do not take a nasopharyngeal swab and thank participant for their time. Otherwise, take a nasopharyngeal swab as directed in the Standard Operating Procedure. |                                                                          |                                                                                                                                                  |  |

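### Outpatient contact before vaccination, which the protocol links to being vaccinated, is not recorded on any cohort form and can be adjusted for only by proxy

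*Protocol*

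**What the plan says.** Section 3.1.1 undertakes to measure factors associated with vaccination and to model the propensity for vaccination from them. The Limitations section, discussing limited vaccine supply, says that "elderly that are sicker and see health care professionals more often are more likely to become vaccinated than those who are healthier".

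Appendix 4b asks for self-rated health and for severe illness in the last year. Item 6 is "Did you have to be hospitalized for any illness in the last year", answered yes or no. The chronic-disease block opens with "Please tell me whether you have been diagnosed by a physician with any of the following conditions", and item 57 asks where care is normally sought. The screening form (3a) records distance to the nearest health center and household coordinates. Visits to a doctor or nurse are counted only in Appendix 4g (item 16), and only within an ARI or SARI episode.

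Section 7.9 gives examples of covariates: variables related to "underlying disease such as age, co-morbidities and distance to health facility". It also plans propensity score matching.

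On case finding, section 7.5.1 says "Health volunteers will also be trained to contact their assigned participants weekly to identify ARI events that they have not been notified of already", with a self-swab to follow. When a very ill participant attends for an ARI or SARI, "the research nurse at the sub-district health center or district hospital will collect a nasopharyngeal swab from the participant".

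**The concern.** Objective 1.1 compares people who were and were not vaccinated by their own and their providers' choice, so it depends on adjusting for why they were vaccinated. Frequency of contact with health services is part of the reason the protocol itself gives, and its outpatient component is not collected.

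This cannot be left to an analysis plan, which can choose among recorded variables but cannot supply one that was never recorded. If frequent attenders differ in influenza risk, or in the chance that influenza is detected, after the recorded covariates are held equal, the adjusted VE will be off by an amount the planned data cannot show.

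**Working it through.** **What the forms capture**

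| Recorded item | What it leaves out |
|---|---|
| Hospitalised in the last year, yes/no (4b item 6) | Outpatient visits; number of admissions |
| Severe illness in the last year, yes/no (4b item 5) | Whether and how often care was sought |
| Physician-diagnosed conditions (4b items 33-48) | Frequency of contact. Limitations adds that people who rarely see a physician may not know their conditions |
| Usual place of care (4b item 57) | Frequency |
| Distance to health center (3a item 11) | Access, not use |
| Visits during an episode (4g item 16) | Measured only after illness onset, and only in people who fall ill |

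The record review in sections 7.5.1 and 7.7 covers COPD visits, visit costs and admissions, not baseline visit frequency.

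**Link to detection.** The facility rule in Appendix 4e is "If answer is no for question 2 and 3, do not take a nasopharyngeal swab", where questions 2 and 3 are cough and difficulty breathing. The community forms (4c, 4d) require cough. Facility attendance is thus a second route with a somewhat wider trigger and a different specimen.

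**Size, as an illustration only.** The plan has no figure for this bias. Its related figure is the cohort size in section 7.1.5. With 6% in the unvaccinated, 3.6% in the vaccinated (VE 40%), 80% power, two-sided 5% and continuity correction, I get 1,327 per group, or 2,654 in total. The stated figure is 2,724, so mine is 2.6% lower.

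Let a and b be the shares of frequent attenders among the vaccinated and unvaccinated. Let R be the ratio of detected influenza in frequent attenders to that in others at equal recorded covariates. Then

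B = [1 + a(R − 1)] / [1 + b(R − 1)], and observed VE = 1 − 0.60 × B.

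From section 7.1.5: true VE 40% and 50% vaccinated. Assumed: 40% of the cohort are frequent attenders.

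- Stronger gradient (assumed): 65% of frequent attenders and 40% of others vaccinated. Overall coverage is 0.4 × 0.65 + 0.6 × 0.40 = 0.50, a = 0.26/0.50 = 0.52 and b = 0.14/0.50 = 0.28.
- Weaker gradient (assumed): 60% and 43.3%. Then a = 0.24/0.50 = 0.48 and b = 0.16/0.50 = 0.32.

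| R (assumed) | Observed VE, stronger | Observed VE, weaker |
|---|---|---|
| 1.2 | 37% | 38% |
| 1.3 | 36% | 37% |
| 1.5 | 34% | 36% |
| 2.0 | 29% | 33% |

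Example, stronger gradient at R = 1.5: B = 1.26/1.14 = 1.105, and VE = 1 − 0.60 × 1.105 = 34%.

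The direction reverses when R is below 1. At R = 0.5 with the stronger gradient, B = 0.74/0.86 = 0.860 and VE = 1 − 0.516 = 48%.

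A separate grid, with a/b of 0.5/0.4, 0.6/0.4 and 0.6/0.3 and R from 1.1 to 2.0, gives observed VE of 39-36%, 39-31% and 38-26%.

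For scale, with 1,362 per group (2,724/2) and no continuity correction, one-year power is 83% at B = 1, 77% at B = 1.05 and 69% at B = 1.10.

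**The case against.** The strongest case against the point has four parts.

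1. **Detection does not depend on care-seeking.** Volunteers contact every participant weekly, with three attempts, and anyone with an unswabbed ARI is told to self-swab at once. People without phones are visited at home, and volunteers help those too ill to swab. The nurse route is described for a participant who becomes very ill, so it follows the acute illness rather than the usual number of visits. Difficulty breathing without cough meets an outcome definition only with fever and hospitalisation (section 3.1.4). If detection alone drove R = 2.0, about half of the detectable events in non-attenders would have to be missed. This largely stands. What remains is that Limitations concedes missed events and forgotten swabs, and that section 3.1.4 says self-swab validity is still being analysed.

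2. **The Limitations sentence describes one group**, sicker and with more contact, set against healthier people, and it leads into selection for the immunogenicity sub-study. A focused campaign with mobile clinics (sections 3.1.2 and 7.6) may also weaken the clinic-contact route. This stands as a reason not to treat contact as a proven separate driver. It does not change the fact that contact is unrecorded.

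3. **Proxies exist.** Diagnosed conditions themselves carry information about contact, and function, insurance and usual place of care can also enter the models. This stands too.

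4. **The covariates in section 7.9 are examples**, and a companion study is to inform the confounders. That is correct, and it is why the gap lies in the data item and not in the covariate list.

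A reader might infer that the primary VE is confounded by a factor the planned data cannot adjust for. The documents do not support that: they show a possibility, partly covered by recorded proxies, with no evidence on its size or sign.

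**Conclusion.** The point holds in a limited form. No cohort form measures outpatient contact before vaccination, although the protocol associates such contact with being vaccinated and promises to measure factors of that kind. Adjustment is by proxy only, so residual confounding of the primary VE is possible. Differential detection is a lesser possibility, held down by weekly contact and self-swabbing.

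The size is unknown. The range of roughly 38% to 29% for a true VE of 40% rests entirely on the assumed share of frequent attenders, the assumed vaccination gradients and R between 1.2 and 2.0. With R below 1 the estimate would rise instead. For R of 1.2 to 1.3 the shift is about 2 to 4 points, which is small beside a one-year 95% interval of about 15% to 58% (1,362 per group, 6% and 3.6%). This is a worthwhile, cheap improvement, not a defect that invalidates the comparison.

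**What to change.** Add one question to Appendix 4b after item 6: the number of visits to a sub-district health center, hospital or clinic during a fixed 12-month window that ends before the 2015 vaccination campaign, for example before 15 May 2015.

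For people already enrolled, take the count for that same window from facility records through the identification number on form 3a (item 7). Alternatively, ask it once at a weekly contact, as section 7.5.3 does for form 4i. The window must be fixed by calendar date. A question about the last 12 months asked at a later contact would count the vaccination visit itself and visits for outcome illnesses.

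Include the count in both the vaccination propensity score and the Poisson/GEE model.

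The cost is one question or one record count per participant and one more covariate. The downside is some recall error, or incomplete records where care was sought elsewhere. No extra visits or participants are needed.
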